### Allocation

Families are allocated to a family club or a waitlist based on a first-come-first-serve principle conditional on their vulnerability classification. Around nine families are allocated to one family club and any extra families will be offered to be on a wait-list for the next round or when another club starts in the area at a later timepoint. The coordinators strive to allocate two or three non-vulnerable families to each family group to make sure that non-vulnerable families are present in all clubs. The coordinators also make sure that families with sufficient Danish language skills are present in each club making it possible for families that do not have Danish as their first language to improve their Danish skills. The discretionary allocation of families, carried out by the coordinators, is made without further regards to family characteristics and thus can be considered as good as random conditional on vulnerability status and Danish language skills. Families that sign up for FCD but live in an area where there is currently no FCD are included in the wait-list control group. Families who have been assigned to FCD are included in the wait-list control group if the start of the FCD is delayed by at least 4 months. Families who have been assigned to FCD but are not able to participate, e.g. because they have other obligations on the assigned day, and families who do not show up for FCD are included in the wait-list control group. The flowchart is presented in Fig. 2.

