**Parent measures**				
Background	Age, gender, language, education	√	√	√
Family	Partner, children	√	√	√
Mental health	Warwick-Edinburgh Mental Wellbeing Scale	√	√	√
Self-efficacy	From general self-efficacy scale	√	√	√
Parental stress	Parental Stress Scale	√	√	√
Family conflicts	Partner, child	√	√	√
Family life	Leisure activities	√	√	√
Family routines	Mealtime, duties, bedtime, homework	√	√	√
Network	Loneliness, practical help, confidants	√	√	√
Parenting competences	From Parent Behavior Inventory	√	√	√
Play	Play with children	√	√	√
Screen time	Parent	√	√	√
Family budget	Worries, budget	√	√	√
Satisfaction	Participation, network		√	

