### Statistical analysis

We analyze the primary and secondary outcomes at post-intervention (T2) and follow-up (T3). We use linear regression for normally distributed outcomes and apply robust standard errors to correct for the correlation between observations participating in the same FCD group. In the case of heavily skewed data, we use non-parametric rank-based tests. To check whether the first-come-first-served principle or the allocation of vulnerable families conducted by the volunteers introduce imbalances in the allocation to FCD and the waitlist control, we test for statistical differences in observable characteristics of the two groups using t-tests. In the analysis of the effectiveness of FCD, the hypothesis tested for each outcome is that the FCD group will score better than the wait-list control group. We test this hypothesis with a binary variable indicating the intervention group. We include variables measured at baseline with indications of imbalances (*p* < 0.1) as control variables and apply two-sided tests with 0.05 significance levels throughout. As all outcomes represent a different aspect of the expected outcome of the intervention we do not consider multiple testing issues. We analyze primary and secondary endpoints according to an intention-to-treat (ITT) principle and handle missing data with multiple imputations. Parametric imputation models are preferred, but in case of severe non-normality or convergence issues, we use predictive mean matching or other non-parametric options. We include the 12-month outcome data for exploratory analyses but can also be used as tools in secondary analyses of missingness. Exploratory analysis of data from all three measurements (T1 - baseline, T2 - 6 months and T3–12 months) will be carried out using mixed-effect regression and possibly latent growth curve analysis. The purpose is to assess the longer-term effects of the intervention and to understand how the psychosocial characteristics of the families involved develop over time. In addition to the primary analysis, we will perform subgroup analyses to examine potential differences between subsets of participants. Hence, we analyze subgroups according to the following characteristics: vulnerability (vulnerable or non-vulnerable families); family composition (single parents or cohabiting parents); the age of target child (< 8 years old or ≥ 8 years old); partner organization (KFUMs Sociale Arbejde, FDF, or KFUM Spejderne); the number of volunteers in the FCD; and the number of sessions attended (dose).

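### Comparability is claimed conditional on vulnerability and Danish skills, but the model adjusts for them only if a baseline t-test gives p < 0.1

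*Protocol article*

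**What the plan says.** The Allocation section describes a steered allocation. "Families are allocated to a family club or a waitlist based on a first-come-first-serve principle conditional on their vulnerability classification". On vulnerability, "The coordinators strive to allocate two or three non-vulnerable families to each family group", in clubs of around nine. On language, "The coordinators also make sure that families with sufficient Danish language skills are present in each club". From this the section concludes that the coordinators' discretionary placement "thus can be considered as good as random conditional on vulnerability status and Danish language skills".

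The Statistical analysis section sets the treatment comparison as follows: "We test this hypothesis with a binary variable indicating the intervention group". To see whether sign-up order or the allocation of vulnerable families has produced imbalance, "we test for statistical differences in observable characteristics of the two groups using t-tests". The covariate rule is then: "We include variables measured at baseline with indications of imbalances (*p* < 0.1) as control variables". No covariate is named as always included, and the two allocation factors are not exempted from the screen. Vulnerability is also listed as a subgroup variable.

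Vulnerability is classified from labor market status and the motivation given at sign-up (Participants). For language, Table 1 lists only a background item, "Age, gender, language, education", at all three time-points.

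**The concern.** The two sections do not fit together. One names the variables on which comparability depends. The other leaves their use to a significance test. The condition in the Allocation section carries no p-value: it requires conditioning on both factors, not conditioning on them when a test happens to reject.

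Vulnerability and Danish skills act as the strata of the allocation. Clubs are steered towards a mix of the two, while nothing steers the mix on the wait-list, so the arms may differ on these factors because of how they were filled. Vulnerability is defined partly by daily stress, loneliness and family conflict, so a relation with a mental well-being scale such as SWEMWBS is very plausible. An imbalance left unadjusted would move the primary estimate.

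**Working it through.** **Planned figure.** Power considerations gives 80 control and 120 intervention families, SMD 0.35, two-sided 0.05, and correlation 0.50 between baseline and post-intervention. With the baseline-adjusted residual SD √(1 − 0.50²) = 0.866:

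- SE = 0.866 × √(1/80 + 1/120) = 0.866 × 0.1443 = 0.125
- power = Φ(0.35/0.125 − 1.96) = Φ(0.84) = 0.80

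The stated 80% reproduces.

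**What the screen detects.** With 120 versus 80 families, p < 0.1 needs an observed difference of about 1.65 × 0.1443 = 0.24 SD. For a binary factor with 70 to 80% prevalence that is about 10 to 11 percentage points.

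**Worked scenario.** Two or three non-vulnerable families in nine is 22 to 33%, midpoint 2.5/9 = 28%. The documents give no wait-list share; 18% is assumed.

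- SE of the difference = √(0.28 × 0.72/120 + 0.18 × 0.82/80) = 0.0594
- threshold = 1.645 × 0.0594 = 9.8 points
- P(missed, given a true 10-point gap) = Φ((0.0977 − 0.10)/0.0594) = Φ(−0.039) = 0.48
- mean observed gap when missed (truncated normal) = 0.10 − 0.0594 × φ(−0.039)/Φ(−0.039) = 0.10 − 0.0594 × 0.824 = 0.051

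Simulating the t-test itself agrees: about half of trials missed, with a mean gap of about 5 points among them.

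**Bias.** Gap × difference in SWEMWBS between vulnerable and non-vulnerable families, assumed 0.5 to 1.0 SD:

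- when missed: 0.051 × 0.5 = 0.026 SD to 0.051 × 1.0 = 0.051 SD, or 7 to 15% of 0.35
- over all trials (bias about zero when the factor is included): 0.48 × 0.026 = 0.012 SD to 0.48 × 0.051 = 0.025 SD

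**Wider range.** Simulation with no true effect, 5,000 trials per scenario, factor prevalence 70% in FCD (all assumed):

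| Prevalence in control | Missed by the screen | Mean bias when missed, factor effect 0.3 to 0.8 SD |
|---|---|---|
| 75% | 80% | 0.01 to 0.02 SD |
| 80% | 52% | 0.015 to 0.04 SD |
| 85% | 19% | 0.02 to 0.05 SD |
| 90% | 2.5% | 0.02 to 0.06 SD |

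Over all trials the screen leaves 0.00 to 0.02 SD. Always including the factor leaves about 0.00. The rejection rate is about 4.5% either way.

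**Cost of always adjusting.** If the factors explain a share R² of the variance in arm, the residual variance 0.75 becomes 0.75/(1 − R²). Power is 79.6% at 1%, 79.2% at 2% and 77.9% at 5%. In the scenario above, overall prevalence is (120 × 0.28 + 80 × 0.18)/200 = 0.24, so vulnerability alone gives R² = 0.10² × 0.6 × 0.4/(0.24 × 0.76) = 1.3%.

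**The case against.** **The screen catches large imbalances.** This stands: a 20-point gap is missed in only about 2.5% of trials. Gaps of 5 to 10 points often pass.

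**The plan does look at this mechanism.** Also true. The balance check is aimed explicitly at the allocation of vulnerable families, and the subgroup analysis gives estimates within vulnerability strata. It would be wrong to say that the plan ignores the issue. The weakness is the tool: non-significance is read as balance.

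**The 120 and 80 may all be vulnerable families.** Recruitment describes the target of 200 in those terms. If the primary analysis were restricted to them, vulnerability would be constant and only the Danish-language part would remain. Statistical analysis states no such restriction and lists vulnerable versus non-vulnerable as a subgroup, so this is a caveat and not a rebuttal.

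**Danish skills are a narrower factor than they look.** Families unable to complete questionnaires in Danish are excluded. That limits the range of the factor but does not remove it from the comparability claim. Its effect is not quantified here and could add to or offset that of vulnerability.

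**The coordinators' quota is not the whole argument for comparability.** The Allocation section also relies on mixed recruitment channels and expects most controls to come from areas without a club. The Discussion calls causal conclusions tentative. A reader might infer that the trial's entire causal case falls with this point; the documents do not support that.

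**Conclusion.** The inconsistency holds on the text alone: the comparability of coordinator-allocated families rests on two named factors that the stated model may leave out. The size is modest. Under the assumed 28% versus 18% shares and a 0.5 to 1.0 SD difference on SWEMWBS, the bias is about 0.03 to 0.05 SD when the gap is missed and about 0.01 to 0.03 SD over all trials, against 0.35. The direction is unknown, because the documents do not say which arm will hold more vulnerable families.

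A reader might infer that missed trials carry the full 10-point gap, which would give 0.10 × 0.5 = 0.05 SD to 0.10 × 1.0 = 0.10 SD, or 14 to 29% of the planned effect. That does not follow. The screen acts on the observed gap, so the trials it misses are mainly those with smaller gaps. Nor does the simulation show an inflated type I error from one such factor. The case for change is that the plan should meet its own condition, and that doing so is nearly free.

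**What to change.** In Statistical analysis, state that vulnerability status, as classified at sign-up, and Danish language enter every effectiveness model regardless of any balance test. The p < 0.1 screen, if kept, then applies only to other variables. If the primary analysis is meant for vulnerable families only, say so; the vulnerability term then drops out.

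For Danish language, use the coordinators' own record if one exists. The article does not show that it does, and Table 1 lists only language, so the T1 language item would otherwise serve as a proxy and should be described as one.

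The cost is one sentence, two degrees of freedom and the small power loss shown in the working (80% to between 79.6% and about 78%). The change does not deal with entry to the control group through areas without a club, a delayed start, inability to attend or failure to show up. Those routes need separate treatment.

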**Fig.2 Fig2:**
[figure not shown]
Study flow chart

The first-come-first-served principle potentially introduces selection issues if first responders differ from later attendees by e.g. being more enthusiastic. The recruitment strategy, involving the use of several channels that target potential families in very different approaches, can to some extent mitigate the selective timing of sign up. The mix of personal recruitment by municipal social workers or local social housing employees with the online recruitment process can introduce some randomness in who signs up when. Also, first responders can be assigned to the control group for other reasons such as no club in their local area, or the family could not participate on the day that the club was offered. We expect that most families are allocated to the control group because they sign up for an FCD in an area where there is not yet any FCD. Therefore, we expect that the potential selection issues introduced by the first-come-first-served principle are minimized.

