### Measures

Table 1 shows the timing of the administration of measures. Socio-demographic characteristics assessed at T1-T3 include the age of the parent, education, occupation, ethnicity, number of children, child age, household status, housing situation, and household economy.

**Table 1 Tab1:** Timing of outcomes – parents

		T1	T2	T3

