## Discussion

This study is a prospective quasi-experimental trial assessing the effectiveness of FCD on parent stress, mental health, development and well-being of parents and children. The study will contribute to the evidence-base of the effectiveness of need-oriented family support programs.

Compared to other research fields, the tradition of rigorous evaluation of interventions’ impact within civil society is rather weak. The voluntary nature of such interventions is an inherent challenge when evaluating impact. Thus, this is a challenge that this study shares with similar studies examining the impact or effectiveness of other voluntary interventions. Voluntary engagement is difficult to control and although the concept is manualized and volunteers are offered a one-day training the intervention highly depends on the engagement and personal qualities of the volunteers. It is not possible and would not be fruitful to demand the volunteers to act strictly according to a manual. Consequently, the study is conducted in a very flexible and accommodating way. The practical execution is streamlined as much as possible but with a high degree of respect for local needs and differences. Therefore, family clubs will wary in terms of what and how they practically carry out the activities. Moreover, family clubs take place in settings with different characteristics such as the degree of ethnic diversity, public housing, and family income. This is likely to cause variation in delivery and receipt of the FCD activities. The study does provide some insight into these differences in the content of the different FCD’s, and the different competencies of the volunteers. The degree of variation may though complicate the identification of effective components of FCD, including characteristics of both volunteers and participants that contribute to FCD being more or less successful.

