Other potential limitations relate to methodological as well as practical challenges. A practical challenge concerns the probability of attrition among participants allocated to the control group; if FCD is perceived as an attractive offer, being assigned to the wait-list with the prospect of being offered the intervention in six months might be difficult to accept. Because we are not able to apply strict random allocation comparability between the intervention group and control group cannot be guaranteed and conclusions about causality are expected to be tentative rather than definitive. On the other hand, the study is conducted in a naturalistic setting, which can be regarded as a strength to represent the setting in which FCD is applied.

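### Most controls are expected from areas without a club, which exchanges selection by sign-up time for selection by place; the stated analysis has no area term and no cluster unit for controls

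*Protocol article*

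**What the plan says.** Under Allocation, a family enters the control group by several routes: the club was full, its start was delayed by at least 4 months, the family could not attend or did not show up, or the family lives where no club exists. The paragraph after Fig. 2 expects the last route to dominate: for most controls the reason given is that "they sign up for an FCD in an area where there is not yet any FCD". From this it concludes that "selection issues introduced by the first-come-first-served principle are minimized". The same section says the coordinators' discretionary allocation "can be considered as good as random conditional on vulnerability status and Danish language skills".

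Statistical analysis tests a binary intervention term, adjusts for baseline variables that show imbalance at p < 0.1, and uses robust standard errors to "correct for the correlation between observations participating in the same FCD group". The baseline characteristics under Measures "include the age of the parent, education, occupation, ethnicity, number of children, child age, household status, housing situation, and household economy". Neither area nor region appears among the listed characteristics, the covariates, the cluster unit or the subgroups.

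The Discussion adds a general caveat that "comparability between the intervention group and control group cannot be guaranteed".

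**The concern.** A family that is a control because its area has no club was not sorted by when it signed up. It was sorted by where it lives. A club needs a venue and volunteers, which the coordinators must find (Recruitment), so areas that have one may differ from areas that do not. The article weighs the first kind of selection and not the second.

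Two things follow. First, a difference between club and no-club areas in parental well-being, or in its trend, would be partly carried by the arm coefficient and read as a programme effect; it could also mask one. Second, controls belong to no FCD group, so the stated robust errors give no handling to correlation among controls from the same area. If such correlation exists, the control-side variance is understated.

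**Working it through.** **Inputs from the article (Power considerations, Statistical analysis):** 80 controls, 120 FCD families, target 0.35 SMD, baseline-to-post correlation 0.50, two-sided alpha 0.05.

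**Assumed, because the article gives no figures:** 60-80% of controls from no-club areas (the text says only that it is most); a club versus no-club difference of 0.1-0.2 SMD; controls spread over 10-20 areas; ICC 0.05-0.10; the baseline score is in the model, as the power statement implies.

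**1. The stated power.** SE = sqrt[(1 - 0.50²) × (1/80 + 1/120)] = sqrt(0.75 × 0.02083) = 0.125. Power = Φ(0.35/0.125 - 1.96) = Φ(0.84) = 0.80. The stated figure reproduces, with independent families and no area effect.

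**2. Bias from place.** Bias = share of no-club controls × area difference left after adjustment. The chance of a significant result when the programme has no effect is 1 - Φ(1.96 - b/SE) + Φ(-1.96 - b/SE).

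*Stable difference in level.* With equal SDs at both times the ANCOVA slope is 0.50, so half the difference remains.
- Low: 0.60 × 0.1 × 0.5 = 0.03; b/SE = 0.24; type I error 5.7%.
- High: 0.80 × 0.2 × 0.5 = 0.08; b/SE = 0.64; type I error 9.8%.

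*Difference that is residual after adjustment, or is in the trend.* Nothing is halved.
- Low: 0.60 × 0.1 = 0.06; b/SE = 0.48; type I error 7.7%.
- High: 0.80 × 0.2 = 0.16; b/SE = 1.28; type I error 24.9%.

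Against the 0.35 target, 0.03-0.08 is 9-23% and 0.06-0.16 is 17-46%.

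**3. Standard errors, taken separately with no area bias.** Take 17 clubs of 7 families (about 120) and m controls per area. The variance the stated method targets is V0 = (0.75/120)(1 + 6·ICC) + 0.75/80. The true variance is V1 = (0.75/120)(1 + 6·ICC) + (0.75/80)[1 + (m - 1)·ICC]. Type I error = 2[1 - Φ(1.96·sqrt(V0/V1))].
- ICC 0.05, 20 areas (m = 4): sqrt(V0) = 0.1323, sqrt(V1) = 0.1375; 5.9%.
- ICC 0.10, 10 areas (m = 8): sqrt(V0) = 0.1392, sqrt(V1) = 0.1611; 9.0%.

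Simulation of the same layout, with each control as its own cluster, gives about 6-10%. With no correlation among controls it gives about 5-6%, so a small part of the excess comes from the limited number of clubs and not from the omission.

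**4. What a comparison within club areas could show.** If 60-80% of the 80 controls drop out, 32 to 16 remain.
- 32 v 120: SE = sqrt[0.75(1/32 + 1/120)] = 0.172; power at 0.35 SMD is 53%.
- 16 v 120: SE = sqrt[0.75(1/16 + 1/120)] = 0.230; power is 33%.

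These are upper limits, because the remaining controls still include families who did not attend and families whose club was delayed.

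**The case against.** The strongest reply is that the article claims little and already hedges. The minimized sentence concerns only the first-come-first-served principle, and within that scope it follows. The trial is labelled quasi-experimental and calls its causal conclusions tentative. Confounding is partial: overflow, delayed-start and non-attending controls come from areas that have a club or are due one, and some no-club areas gain one later. Ethnicity, housing situation and household economy are measured per household and can enter through the p < 0.1 rule. Sign-up area is administrative information, so its absence from a list of survey items does not show that it goes unrecorded.

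All of this stands and limits the point. What it does not supply is a consideration of place where the article reasons about selection, a model term that follows from the known allocation route whatever a significance test says, or a cluster unit for controls. Household covariates do not capture purely contextual differences, and the general caveat changes nothing in the analysis.

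Three stronger readings are tempting and are not supported:
- That the article claims selection has been removed altogether. It speaks only of selection by sign-up order.
- That "can be considered as good as random conditional on vulnerability status and Danish language skills" contradicts the Discussion's caveat. The first describes the coordinators' discretionary allocation; the no-club rule is stated separately after it, and the caveat concerns the whole trial. The scopes differ.
- That the Discussion shows club and no-club areas to differ. It says "family clubs take place in settings with different characteristics such as the degree of ethnic diversity, public housing, and family income", which compares clubs with one another. A difference between club and no-club areas is plausible but not documented.

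**Conclusion.** The point holds in a limited form. By the article's own expectation, residence in a no-club area is the main route into the control group. The inference drawn from this covers sign-up timing only and leaves selection by place unconsidered. The stated analysis has no area term and treats controls from one area as independent.

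How much this matters depends on inputs the article does not give. On the assumed ranges, a stable area difference produces a modest distortion. The effect becomes serious only at the upper end, where the difference survives baseline adjustment or lies in the trend. The clustering omission is a separate and smaller matter. A reader might infer that this is the main threat to the trial's causal reading; no ranking supports that, and the rule moving assigned families who do not attend into the control group is an obvious rival.

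**What to change.** **Wording.** Keep the minimized statement but limit it expressly to sign-up timing. Add that areas with and without a club may differ, and that the claim of near-random allocation does not cover the no-club route.

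**Data.** Keep sign-up area and recruitment round for every family. Most families apply for a specific club, so area should be recoverable.

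**Primary model.** Enter region and recruitment round in every outcome model whatever their balance p-values. Cluster the robust errors by sign-up area in both arms, with a small-sample correction (CR2 with Satterthwaite degrees of freedom). Fixed effects for each area are not suggested: controls in areas with no FCD family carry no within-area contrast and would in effect be discarded.

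**Sensitivity analysis.** Prespecify a comparison limited to areas and rounds where a club ran, of FCD families with families wait-listed because the club was full. Report it as low-powered (at most about 33-53% at 0.35 SMD) and as still open to selection by sign-up time.

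**Cost.** Text changes, one extra model, slightly wider intervals and a few degrees of freedom: five regions and four intakes take 4 + 3 = 7. Region terms do not remove differences between localities within a region, so the package reduces and probes area confounding without removing it.
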